### 3.2. Data Collection

Quantitative outcome measures (described in Section 2.5) are administered on paper at baseline (T0) and post-intervention (T2, Week 12). Post-intervention assessments are conducted by trained coordinators/assessors blinded to group allocation; blinding is maintained by: (1) providing assessors only the participant study code (no group information); (2) restricting assessor access to baseline data or randomization records; and (3) ensuring assessors have no knowledge of intervention attendance or session fidelity ratings. Completed questionnaires are entered into a secure electronic with double-entry verification. Missing data patterns are examined; Section 2.7 specifies handling strategies.

Weekly Journaling (Intervention Group Only): Intervention group participants complete standardized written reflections (5–10 min) at the end of each session using prompts addressing: breath/embodiment, emotional states, movement awareness, meaning-making, and perceived changes across weeks (prompts detailed in Supplementary File S3 [27]). Journal forms are collected weekly by facilitators and maintained in secure storage. A purposive sample of journal entries (selected from Weeks 1, 4, 8, and 12, plus entries with maximum phenomenological variation) is analyzed for thematic patterns regarding embodied experience, affective change, and perceived transformation using Reflexive Thematic Analysis with phase-specific coding (Weeks 1–4, 5–8, 9–12; detailed methodology in Supplementary File S3 [27]). Two independent coders will analyze qualitative data using structured coding protocols; differences are resolved through consensus discussion. Control group participants do not complete journaling; they complete quantitative assessments only (T0 and T2).

Semi-Structured Interviews (Intervention Group Subsample): Approximately 30 intervention group participants are selected via maximum variation sampling (Section 2.7). Semi-structured interviews are conducted by trained research staff not involved in intervention delivery at mid-intervention (T1, Week 8) and post-intervention (T2, Week 12) in private, quiet locations at the respective dance schools. Each interview is approximately 20–30 min in duration and is audio recorded after participant consent. The interview guide (Supplementary File S3 [27]) addresses: embodied experience and somatic awareness, emotional awareness and regulation, movement identity and creative expression, meaning-making, perceived changes (psychological, physical, social), and program structure and safety.

Interview data will be analyzed using Interpretative Phenomenological Analysis (IPA) following the six-step procedure [40]: (1) reading and re-reading transcripts; (2) initial line-by-line coding; (3) developing emergent themes within each case; (4) searching for connections across themes within cases; (5) repeating steps 1–4 for each interview independently; and (6) cross-case analysis to identify superordinate themes and patterns (Supplementary File S3 [27]).

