## 2. Experimental Design

### 2.1. Trial Design

This study has been prospectively registered on ClinicalTrials.gov (NCT07262177; brief title: Dance-Mindfulness Intervention for Well-Being in Recreational Adults-DanceMind) and approved by the institutional Research Ethics Committee (IEC, DPESS, UTH 4-2/2.4.2025; Supplementary File S8 [27]). The protocol follows SPIRIT [28,29], TIDieR [30], and CONSORT standards [31].

This is a two-parallel group randomized controlled trial (RCT). The intervention group receives a 12-week integrated dance-mindfulness protocol grounded in polyvagal theory, motor learning science, and embodied phenomenology. The control group continues regular recreational dance activities without mindfulness or somatic-reflective components. Participants are randomly allocated 2:1 (intervention: control) using computer-generated randomization with allocation concealment.

Quantitative assessments occur at baseline (T0) and post-intervention (T2 Week 12). Qualitative data collection occurs at mid-intervention (T1 Week 8) and post-intervention (T2 Week 12). This mixed-methods design permits concurrent testing of quantitative psychological outcomes (life satisfaction, subjective happiness, psychological distress, mindful attention, leisure involvement) and qualitative embodied experiences (somatic awareness, nervous system resilience, technical confidence, creative expression, relational belonging, meaning-making).

All procedures follow ethical principles outlined in the Declaration of Helsinki. Written informed consent is obtained prior to enrollment. Participants have the right to withdraw at any time without consequence. Personal data are stored securely in encrypted databases. Each participant receives a unique study code; identifying information is separated from research data. All facilitators hold CPR/First Aid certification and mindfulness training. Session checklists document adverse events. If a participant reports intense psychological distress, the study is suspended for that individual with clinical referral provided. Facilitators are trained to recognize signs of emotional dysregulation and provide immediate basic containment (quiet space, grounding breath), without attempting psychological exploration. Control group participants receive delayed access to the intervention after post-intervention assessment (Supplementary Files S1–S8 [27]).

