### 2.7. Data Collection and Analysis

Self-report questionnaires (SWLS, DASS-21, MAAS, SHS, LIS) are administered on paper at baseline (T0) and post-intervention (T2) by trained site coordinators in quiet studio environments (~20–30 min per assessment). Questionnaires are entered into a secure electronic database with double-entry verification.

Demographic and baseline characteristics are summarized using descriptive statistics (means, standard deviations, medians, frequencies, percentages). Shapiro–Wilk tests and visual inspection (Q-Q plots, histograms) assess normality for all primary outcome variables. Between-group demographic comparisons use independent-samples *t*-tests (continuous) and chi-square tests (categorical). Internal consistency is assessed using Cronbach’s alpha (α ≥ 0.70); test–retest reliability via intraclass correlation coefficients (ICC ≥ 0.70) in the control group.

If normality is met (Shapiro–Wilk *p* > 0.05), a 2 (Group) × 2 (Time) mixed-model repeated-measures ANOVA is conducted on each primary outcome, with Bonferroni-corrected α = 0.01 to control Type I error. Alternative testing via MANOVA (Wilks’ Lambda, α = 0.05) proceeds to univariate ANOVAs if significant. ANCOVA with T0 baseline covariates is conducted with Levene’s test assessing homogeneity of variance; if violated (*p* < 0.05). Effect sizes and 95% confidence intervals are reported.

If normality is violated (Shapiro–Wilk *p* < 0.05), non-parametric tests will be used: Friedman’s test (within-group time effects), Mann–Whitney U (between-group comparisons), Wilcoxon signed-rank test (within-group pre–post). Post hoc pairwise comparisons use Bonferroni-corrected alpha. Pearson correlations (Bonferroni-corrected) for normally distributed variables; Spearman’s rank-order correlations for non-normal variables. Correlations ≥ |0.30| are highlighted. Quantitative analyses use IBM SPSS v. 28; results are reported per CONSORT guidelines [31] with summary statistics, 95% confidence intervals, and effect sizes. Significance level: α = 0.05 (two-tailed) unless otherwise specified (Bonferroni-corrected α = 0.01).

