### 3.5. Intervention Facilitator Qualifications and Training

Intervention sessions are delivered by certified modern dance educators meeting the following minimum qualifications: (1) bachelor’s degree or equivalent certification in dance or somatic movement; (2) minimum two years prior teaching experience with recreational adult populations; (3) formal training in mindfulness-based practices (MBSR certification, 200 h yoga teacher training, or safety-aware somatic training). Trauma-informed training is optional for facilitators with relevant background but not required, as the protocol maintains clear pedagogical boundaries; and (4) current CPR/First Aid certification. Prior to participant contact, each facilitator completes a 12 h standardized training module based on the Intervention Protocol Manual (Supplementary S1 [27]) and participates in 1–2 mock teaching sessions observed by the principal investigator, with written feedback incorporated before first participant session delivery.

Prior to each session, facilitators complete environmental standardization checklists documenting: studio temperature (17–22 °C), illumination (300–500 lux, LED flicker-free), acoustic baseline (≤50 dB), floor conditions (sprung or semi-sprung surface), room dimensions and participant spacing (3.5–4.0 m^2^ per participant), and confirmation of clear emergency exit pathways and visible first aid kit location (detailed specifications in Supplementary File S2 [27]).

Session attendance is recorded by the facilitator at each weekly session. If a participant misses a session, the site coordinator contacts them within 48 h to understand reasons and reschedule a make-up session if feasible, preferably within the same phase. Participants missing more than two consecutive sessions receive additional follow-up contact to assess barriers and provide support (childcare resources, transportation assistance, schedule accommodation).

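### Site coordinators who administer the week 12 questionnaires are declared blind to arm and attendance, yet the same role contacts intervention absentees, so assessor blinding is not assured as written

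*Protocol article*

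**What the plan says.** Four places in the protocol article bear on this point.

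- **Section 2.7** says who hands out the five questionnaires: they "are administered on paper at baseline (T0) and post-intervention (T2) by trained site coordinators in quiet studio environments".
- **Section 3.2** says of week 12: "Post-intervention assessments are conducted by trained coordinators/assessors blinded to group allocation". It lists three safeguards: assessors see only the study code, their access to baseline data and randomization records is restricted, and the third is "ensuring assessors have no knowledge of intervention attendance or session fidelity ratings".
- **Section 3.5** describes attendance follow-up: "Session attendance is recorded by the facilitator at each weekly session". Then: "If a participant misses a session, the site coordinator contacts them within 48 h to understand reasons and reschedule a make-up session if feasible". Make-ups are preferably placed within the same phase of the programme. A further step follows: "Participants missing more than two consecutive sessions receive additional follow-up contact to assess barriers and provide support"; the document does not say who makes that contact.
- **Section 2.4** states, in describing randomization, that recruitment staff and outcome assessors stay blind to allocation.

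For the comparator, Section 2.1 says: "The control group continues regular recreational dance activities without mindfulness or somatic-reflective components".

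**The concern.** The role that must not know attendance (Section 3.2) is, through Section 2.7, the same role that must act on attendance (Section 3.5). A coordinator who has asked a participant why a session was missed, and has booked a replacement, knows that this participant is in the intervention arm and has been absent. A study code on the form does not undo that knowledge when the coordinator has dealt with the participant in person.

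At stake is whether the trial can claim assessor blinding. A report that follows Sections 2.4 and 3.2 would present it as a property of the trial. All five primary outcomes are self-reports by participants who know their arm, so masking at administration is the only masking claimed when outcomes are collected. If it is absent for many participants in one arm, readers would credit the trial with a protection that its own procedures undo.

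**Working it through.** The plan gives no figure on this point, so there is none to reproduce. The check compares roles; a short calculation then shows how far the problem could reach.

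**Step 1: who does what**

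| Task | Role named | Section |
|---|---|---|
| Administers questionnaires at T0 and T2 | Site coordinators | 2.7 |
| Must be blind to allocation and attendance at T2 | Coordinators/assessors | 3.2 |
| Records attendance | Facilitator | 3.5 |
| Contacts absentees, arranges make-ups | Site coordinator | 3.5 |
| Extra contact after more than two consecutive absences | Not named | 3.5 |

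Rows 1, 2 and 4 name the same role. Rows 2 and 4 cannot both hold for one person.

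**Step 2: does the contact reveal the arm?** Yes. The sessions in Section 3.5 are led by the intervention facilitators and belong to programme phases, which exist only in the intervention (Section 2.6). Controls carry on with their usual dance activities and have no study session to miss or make up.

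**Step 3: is a separation of tasks stated anywhere?** Not in the text shown. Section 3.2 does state one for the interviews, which go to research staff who take no part in delivering the intervention. It states none for the coordinators at T2. Section 2.4 expects only 1–2 participating schools, so the pool of coordinators is probably small, though its size is not given.

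**Step 4: how many participants could be unmasked?** Inputs from the document: 12 weekly sessions (Section 2.6) and 76 intervention participants (Section 2.4). Assumed: attendance probability *a* per session, equal for everyone and independent across sessions.

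P(at least one absence) = 1 − *a*^12; expected number = 76 × P.

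| Assumed *a* | 1 − *a*^12 | Of 76 |
|---|---|---|
| 0.98 | 21.5% | about 16 |
| 0.95 | 46.0% | about 35 |
| 0.90 | 71.8% | about 55 |
| 0.80 | 93.1% | about 71 |
| 0.70 | 98.6% | about 75 |

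The protocol asks participants to commit to at least 8 of 12 sessions (Section 2.3), so some absence is anticipated. The table counts participants whose arm would become known to the coordinator role. It does not measure bias in any outcome.

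**The case against.** Several points on the other side are fair.

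**Roles, not people, are named.** Different coordinators could do the two tasks, and Section 3 calls itself an overview and refers to supplementary files that are not shown. A reader might infer from the overlap that the blinding does not exist at all. The documents do not support that: they name a role, and an absence contact directly unmasks only participants who miss a session. It does stand that the text shown makes no separation, so following it as written breaks the third safeguard.

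**Some tempting details go beyond the text.** Section 3.5 says that absentees are contacted; it does not say by telephone. The practical support belongs to the later contact, for which no one is named. Nothing shows that coordinators have a stake in the result. Section 3.2 restricts access to baseline data, and handing out the baseline forms is not the same as having access to those data, so a second contradiction on that ground would be weak.

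**The effect on outcomes is probably limited.** Participants fill in paper forms, the assessor rates nothing, and Section 3.7 requires the same battery and standard administration in both groups. Participants' knowledge of their own arm is the larger source of bias, and reassigning tasks leaves it unchanged. This objection stands, and it keeps the point to a claimed safeguard that the plan does not secure.

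**The attendance rates are assumed.** If absences cluster in a few people, fewer participants than tabulated would be unmasked. This also stands, which is why a range is shown.

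**There may be another route to unmasking.** After randomization, Section 2.4 provides arm-specific disclosure, consent and guidelines without naming the staff who give them. Moving absence contact alone may therefore not make coordinators blind.

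**Conclusion.** The concern holds in a limited form. Sections 2.7, 3.2 and 3.5 conflict over the site coordinator, and the statement in Section 2.4 about outcome assessors is affected as well. As written, assessor blinding is not assured, because each absence contact discloses arm and attendance to the role that administers T2.

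The reach depends on attendance, which the documents do not give. With equal, independent attendance across sessions it is about 46% of the 76 intervention participants at 95%, 72% at 90% and 93% at 80%. This rests on the coordinators who contact absentees also being those who administer T2, which the text implies by role but does not state for individuals. The documents support no estimate of resulting bias in the five questionnaires. The matter should be corrected because the blinding statement would be carried into the trial report and the correction is cheap.

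**What to change.** Either of two changes resolves the conflict.

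1. Assign absence contact and make-up scheduling to the facilitator, who already records attendance.
2. Keep the contact with a coordinator, but state that T2 is administered only by existing staff who have no role in absence contact.

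Under either option, say who handles the arm-specific disclosure and guidelines after randomization, so that this task does not fall to those who administer T2. If neither can be arranged, or if fieldwork has passed the point where it would help, limit or withdraw the assessor-blinding statements in Sections 2.4 and 3.2.

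In every case, state that the five primary outcomes are self-reports by participants who know their arm, and that assessor masking covers questionnaire administration only and does not remove participant-side bias. Do not add a claim of masked data entry: the protocol describes double entry and range checks, not masking.

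The cost is small. Under the first option facilitators take on some contacts; under the second, existing staff duties are divided differently; under the last, only the wording changes. Sample size, visits and instruments stay as they are.

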### 3.3. Study’s Intervention Protocol

The 12–week dance mindfulness intervention was structured as a phased, component-based protocol delivered through weekly 90–100 min sessions, organized across three developmental phases (Phase 1: Foundational Weeks 1–4; Phase 2: Embodied Exploration Weeks 5–8; Phase 3: Expressive Integration Weeks 9–12) and comprising eight standardized components designed to integrate nervous system regulation, motor skill development, and embodied meaning-making within ISTD modern dance syllabi [26]. Each session follows the standardized eight-component protocol detailed in Supplementary Files S1 [27]:Warm-up and breath grounding (9–10 min);Technical dance work (14–15 min);Conditioning and strength work with nervous system awareness (9–10 min);Break/transition and nervous system settling (4–5 min);Rhythm and improvisation (8–9 min);Choreographed dance sequences (15–17 min);Cool-down and reflective integration (8–9 min);Phenomenological journaling (10–20 min, flexible duration).

Component 1: Warm-Up and Breath Grounding (9–10 min).

Component 1 is a 9–10 min warm-up establishing embodied presence and nervous system readiness through progressively complex breath-movement integration across three four-week phases. Phase 1 (Weeks 1–4) establishes parasympathetic baseline through synchronized nasal breathing (4-count pattern) with gentle arm movements, light rhythmic activation, and joint mobility sequences. Nasal breathing activates nitric oxide production in paranasal sinuses, enhancing oxygen utilization and reducing chemosensitivity to CO_2_, key mechanisms for parasympathetic engagement [18]. Joint mobility and sensory-kinetic awareness develop interoceptive capacity, allowing participants to access sources of evaluation based on felt sensation rather than external perfectionistic criteria [44]

Phase 2 (Weeks 5–8) develops sympathetic–parasympathetic balance by adding coordinated leg extensions, multi-directional stepping (invisible cross patterns), and elevated-heart-rate activities while maintaining nasal breathing. This trains the nervous system to sustain sympathetic mobilization while maintaining parasympathetic baseline, a critical resilience capacity [8,18]. Learning strategies embedded in facilitator cuing support autonomy and reduce perfectionistic cognitions [44].

Phase 3 (Weeks 9–12) achieves embodied automaticity by weaving all movements into one continuous 7–8 min sequence. Participants execute complex motor patterns automatically while maintaining nervous system coherence, demonstrated by steady heart rate, relaxed presence, and uninterrupted nasal breathing. Dance and movement are recognized as neural exercises that shift affective states within a safe context, optimizing mental and physical health [45].

The three-phase progression mirrors motor learning stages [14]: cognitive (Phase 1, conscious effort), associative (Phase 2, coordinated integration), and automatic (Phase 3, effortless execution) (Table 2). Facilitator language continuously signals safety via warm presence and explicit nervous system cuing, activating the social engagement system and supporting parasympathetic dominance throughout [8]. This approach operationalizes vagal efficiency, the dynamic effectiveness of the vagal brake in regulating heart rate and metabolic output to match environmental and situational demands [8,45].

Component 2: Technical Dance Work (14–15 min)

Phase 1 (Grade 2) establishes body literacy (the ability to identify and reference internal sensation) creating an interoceptive foundation for technical development [46]. Dancers learn basic patterns while optimizing motor synergies and reducing unnecessary muscle tension [47]. Phase 2 (Grade 3) deepens proprioceptive awareness through enhanced complexity, operationalizing how explicit and implicit motor sequence learning occur simultaneously [12,13]. Participants consciously recall movements while implicit systems optimize motor efficiency. Facilitator cuing emphasizes interoceptive feedback rather than external form correction [46]. Phase 3 (Grade 4) integrates embodied self-awareness into authentic expression [23]. Complex sequences become vehicles for the dancer’s voice. Transfer learning principles enable Grade 3 to Grade 4 compatibility through shared movement transitions [13], demonstrating that technical mastery emerges from interoceptive awareness, not perfectionistic replication [23] (Table 3).

Component 3: Conditioning and Strength Work (9–10 min).

Phase 1 (Weeks 1–4) develops foundational embodied awareness during light exertion, teaching the nervous system that effort and parasympathetic presence coexist. Participants learn to breathe through work rather than against it, establishing an interoceptive baseline where sensation-awareness precedes physical adaptation [48]. Phase 2 (Weeks 5–8) deepens nervous system flexibility through rhythmic endurance and oscillation between effort and recovery, demonstrating how the body can sustain challenge while maintaining regulatory access [9]. Participants consciously regulate intensity via breath-monitoring while implicit motor systems optimize efficiency. Facilitator cuing shifts from “work harder” to “what is your breath telling you?” Phase 3 (Weeks 9–12) integrates vagal efficiency (the capacity to meet complex demands while maintaining parasympathetic access) through sustained whole-body effort under controlled intensity [9]. Technical strength becomes clear, serving embodied resilience and nervous system coherence [49]. Participants experience, directly, that they can sustain intensity while staying regulated; this shift in neuroception (the nervous system’s implicit detection of safety) is the core mechanism of trauma recovery [9,48] but, here, it enables optimal flow states in recreational movement practice (Table 4).

Component 4: Nervous System Settling and Break (4–5 min).

Phase 1 (Weeks 1–4) establishes parasympathetic reactivation following moderate exertion, teaching the body that intensity naturally resolves into calm. Participants practice sustained parasympathetic engagement through gentle grounding, developing interoceptive confidence in the nervous system’s capacity to self-regulate downward [17]. Phase 2 (Weeks 5–8) deepens parasympathetic recovery through rhythm and vagal tone restoration, demonstrating the nervous system’s oscillatory capacity and the transition from sympathetic arousal to parasympathetic dominance [11]. Heart rate variability (HRV) returns toward baseline as recovery progresses; facilitator cues emphasize interoceptive confirmation of this shift (“Feel your heartbeat slowing… feel your breath deepening…”). Phase 3 (Weeks 9–12) integrates embodied belonging and collective nervous system coherence through co-regulated presence, where participants experience their individual nervous system settling within the group’s shared regulation [10]. This “feeling felt” by the group reinforces the ventral vagal pathway and establishes relational nervous system healing. Recovery is complete when participants’ interoceptive baseline has reset and parasympathetic dominance is confirmed via visible calm and stable breath [19,50] (Table 5).

Component 5: Rhythm and Improvisation (8–9 min).

Phase 1 (Weeks 1–4) introduces foundational rhythm awareness through structured, minimally improvised movement, establishing intrinsic motivation through novelty and autonomy. Participants explore rhythm within contained parameters, developing felt sense of pulse and timing while maintaining a clear skill-challenge balance [51]. Phase 2 (Weeks 5–8) deepens flow state conditions through guided improvisation with increasing creative autonomy, where implicit learning systems optimize movement generation while attention focuses on embodied expression. Flow emerges when challenge and skill are balanced at moderate-to-high levels; participants experience loss of self-consciousness and merging of action-awareness [20]. Phase 3 (Weeks 9–12) integrates full improvisational engagement with optimally challenging creative tasks, where flow becomes dominant and participants experience absorption, full task engagement with low self-referential thinking [22,51]. Improvisation serves as both an anxiety-reduction tool and a pathway to embodied authenticity; through voluntary creative choices, participants access intrinsic motivation and experience the cascade of neurochemical states (dopamine, norepinephrine activation) that accompany sustained flow [20,21] (Table 6).

Component 6: Choreographed Dance Sequences (15–17 min).

Phase 1 (Weeks 1–4) introduces foundational choreographic learning through motor sequence acquisition, where declarative knowledge (step-by-step instructions) builds individual competence and somatic confidence. Participants develop beta oscillations in motor cortices associated with early learning; movement remains cognitively demanding but increasingly fluent [12]. Phase 2 (Weeks 5–8) deepens motor sequence consolidation through small-group collaborative movement, where implicit learning systems bind individual elements into skilled behavior while attention transitions from “how” to “why” and “with whom.” Ensemble presence emerges as participants experience synchronized nervous systems, inter-brain resonance where individual regulation supports collective coherence [9]. Phase 3 (Weeks 9–12) integrates full choreographic mastery with embodied authenticity, where automaticity permits genuine relational presence and ensemble artistry. Participants experience somatic knowledge acquired through 8 weeks of integrated practice; movement becomes “second nature”, a manifestation of the seven attitudinal factors of mindfulness (non-judging, patience, beginner’s mind, trust, non-striving, acceptance, letting go) embedded in choreography [52]. Ensemble becomes the vehicle for experiencing collective flow, where individual skill-challenge balance within group synchronization produces optimal task engagement and merging of action-awareness [12,15] (Table 7).

Component 7: Cool-Down and Reflective Integration (8–9 min).

Phase 1 (Weeks 1–4) establishes foundational cool-down through gentle movement and guided body scan, introducing participants to basic interoceptive awareness and parasympathetic settling. The body scan meditation, attending to sensations from feet to crown, activates the “sixth sense” (vertical integration via interoception) while facilitating memory consolidation of the session’s somatic learning through systematic attention to embodied sensation [52,53]. Phase 2 (Weeks 5–8) deepens cool-down through expanded stretching and reflective embodied awareness, where participants develop capacity to notice both sensations and emotions present in the body. Embodied reflection (attending to body phenomenologically through Merleau-Ponty’s lens) reveals how the body is the site where consciousness meets world, where hidden assumptions about our experience can surface through careful, embodied attending [54]. Phase 3 (Weeks 9–12) integrates full reflective embodied practice, where participants experience the seven attitudinal factors of mindfulness through cool-down: non-judging (observing sensations without evaluation), patience (allowing release to unfold), beginner’s mind (approaching body anew each session), trust (in natural settling), non-striving (releasing effort), acceptance (of what arises), and letting go (of tension and narratives) [52]. (Table 8) Neural and relational integration mutually support one another; as participants consolidate somatic memories through body scan and reflective practice, their individual nervous system integration simultaneously enables interpersonal regulation and collective well-being [10,53].

Component 8: Phenomenological Journaling (10–20 min).

Phase 1 (Weeks 1–4) introduces foundational narrative-emotional meaning-making through guided journaling prompts focused on individual nervous system learning: “What did your body discover today?” Participants develop capacity to construct coherent narratives of their sensorimotor experience; writing consolidates learning through repeated re-representation of embodied events as language [55]. Phase 2 (Weeks 5–8) deepens journaling to include relational and emotional integration, where narrative-emotion process markers emerge: participants move from “Same Old Storytelling” (habitual narrative) through “Inchoate Storytelling” (tentative new narratives) toward “Discovery Storytelling” (transformed meaning-making) [56]. Phase 3 (Weeks 9–12) integrates full phenomenological reflection across four dimensions: individual transformation, relational attunement, spatial inhabitation, and social belonging. Participants practice embodied reflective practice, attending to how esthetic experience lived through movement translates into articulated meaning through written reflection [25,57]. Journaling serves as both memory consolidation mechanism (translating implicit motor learning into explicit declarative memory) and meaning-making vehicle where participants construct coherent narratives of their developing sense of self through repeated cycles of embodied experience and reflective articulation [55,58] (Table 9).

